## Study AIMS

### General and specific aims

The *2-Brain Regulation to Achieve Improved Neuroprotection during Early Development* (2-BRAINED) research project is funded by the Italian Ministry of Health under the Ricerca Finalizzata 2021 program (research line: Giovani Ricercatori, project code: GR-2021-12375213). It is aimed to assess brain-to-brain co-regulation patterns in dyads of VPT infants and their caregivers and further explore how an early VF intervention may facilitate specific inter-brain regulatory indices.

The first specific aim (Aim 1) is to assess the presence of statistically significant differences in a set of brain-to-brain co-regulation indices—primarily, PLV measure—between dyads of caregivers and VPT compared to FT infants. Previous research gave evidence of specific markers of lower co-regulation in behavioral synchrony (Montirosso et al., 2010), physiological coupling (Feldman and Eidelman, 2007; Porges et al., 2019), and neuroendocrine attunement (Provenzi et al., 2019) in dyads of VPT infants during the first year of life. Consistently, we hypothesized that VPT infants and their caregivers would show less strong brain-to-brain co-regulation indices compared to dyads of FT counterparts at 9 months (corrected age for prematurity, CA).

The second specific aim (Aim 2) is to investigate the effect of an early VF intervention for parents of VPT infants on the selected indices of brain-to-brain co-regulation at 9 months CA. By comparing EEG-hyperscanning-derived indices of inter-brain coupling between dyads of VPT infants exposed to the VF intervention and dyads exposed to care as usual during the 3 months following NICU discharge, we hypothesize to describe greater brain-to-brain co-regulation in the former group.

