**Figure 2 fig2:**
[figure not shown]
Study design. NICU, neonatal intensive care unit; VF, video-feedback intervention; CU, care as usual; CA, corrected age.

The parent and infant signals will be pre-processed separately with the same steps and parameters for both. First, data filtering will be performed with the application of a bandpass 1–30 Hz filter as the planned analyses (see below) will be conducted on the lower (theta and alpha) frequency bands. Subsequently, flat and outlier channels will be detected using the Neonatal EEG Artifact Removal (NEAR) plugin (Kumaravel et al., 2022) and retained (i.e., put in a separate temporary matrix) for later interpolation. Dyads in which at least one of the members displays a signal with more than 15% (*N* > 5) of flagged channels will be excluded from further analyses. The EEG signal from all non-flagged channels will undergo noise correction through the artifact subspace reconstruction (ASR; Chang et al., 2020), with burst criterion (k) set at 10; subsequently, analysis of the components of the signal will be performed through the independent component analysis (ICA; runica function with default settings), producing as many components as the number of good channels. The resulting components will be then classified through the ICLabel (Pion-Tonachini et al., 2019) plugin. Every component flagged as having a 50% or more probability of being an ocular artifact will be rejected. At this stage, the matrix containing the flat and outlier channels will be re-merged with the EEG matrix, and the bad channels will be interpolated through spherical interpolation using the pre-processed signal. The signal will be then re-referenced to the average signal of the channels and split into three different sets containing each phase of the experimental procedure (Play, Still-Face, and Reunion): Each of these sets will be subsequently segmented into 1,000 ms epochs avoiding overlaps. Bad data segments containing residual artifacts in each of the three phases will be identified. All segments in which at least one of the target channels used for estimates of dyadic co-regulation (see below) displays a voltage exceeding ±150 μV (Debnath et al., 2020) will be marked as rejected. The rejected epochs in the infant’s and parent’s signals will be merged to obtain the final pool of rejected epochs for the dyad. This ensures that all the rejected epochs for one interactive member of the dyad will be similarly mirrored for the other partner. Dyadic data will undergo further analyses if their signal contains at least 30 good epochs in both the Play and Reunion phases; if this criterion is not met, their signal will undergo manual epoch rejection performed by an expert EEG coder. In case after the manual epoch rejection, the dyad will result having less than 30 good merged epochs in at least one of the FFSF episodes, the signal will be excluded from further analyses.

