
#### Estimating indices of inter-brain co-regulation

Several inter-brain synchronization indices have been proposed so far to estimate the coupling between two brains (Czeszumski et al., 2020). Since there is still debate on the appropriateness of each inter-brain synchronization measure, we plan to compute and compare several indices (see Table 4). To further check for spurious findings and gather stronger evidence that the obtained co-regulation estimations are not artifact production, we will compare the synchronization indices obtained from the real dyads to surrogate data generated by randomly pairing mothers and infants from different dyads.

**Table 4 tab4:** Indices of inter-brain co-regulation adopted in the 2-BRAINED study.

Index	Description	Notes	Reference
Phase-Locking Value (PLV)	Frequency-specific transients of phase locking independent of amplitude. The value ranges from 0 to 1: values closer to 0 indicate random signals with unsynchronized phases; values closer to 1 indicate stronger coupling between the two signals.	While previous studies focused mainly on infant frequency bands, cross-frequency PLV indices will be obtained for the purposes of the 2-BRAINED study.	Lachaux et al. (1999); Canolty and Knight (2010)
Imaginary Coherence (ICoh)	Computed through spectral density (power) of each participant and cross-spectral density between them to estimate the average phase difference and consistency of phase difference synchronization.	ICoh is expressed as a complex number: the real part represents how much the coherence is driven by instantaneous interactions; the imaginary part shows how much the coherence is based on lagged interactions.	Dikker et al. (2021); Turk et al. (2022)
Amplitude-Amplitude Coupling (AAC)	Expressed as Pearson’s correlation coefficient between normalized power time courses of the two signals.	Amplitude coupling was suggested as a valid alternative to phase coupling for three main reasons: amplitude changes are more easily estimated; amplitude modulations are more extensively characterized across EEG studies; amplitude modulations are more sensitive to neural coupling phenomena non-detectable with other phase-related measures.	Haresign et al. (2022); Koul et al. (2023)

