### Statistical power and sample size estimates

The sample size has been estimated according to over-arching Aim 2, setting parameters as follows: medium effect size, *f* = 0.25, *alpha* = 0.05, *beta* = 0.20, number of groups = 3 (VPT-VF, VPT-CU, and FT). The procedure yielded a total sample size of 159 subjects (53 subjects per RCT arm). Nonetheless, considering the longitudinal nature of the study and the attrition rate related to EEG tasks with infants, an oversampling of *n* = 80 (~ +50%) subjects per RCT arm was planned to secure the minimum sample size for appropriately powered statistical analyses.

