### Plan of statistical analyses

#### Preliminary analyses

##### Specific aim 1

General linear models (GLMs) will be carried out to compare VPT and FT dyadic brain-to-brain co-regulation indices during the experimental procedure phases. Theoretically relevant (e.g., gestational age) and statistically identified (e.g., any variable significantly linked with the outcome variables) confounding variables will be controlled for in the analytical model.

##### Specific aim 2

Separate analyses of variance (ANOVA) will be used with dyadic brain-to-brain co-regulation indices as the dependent variable and groups (FT, VPT-VF, and VPT-CU) as the independent variable. Theoretically relevant (e.g., gestational age) and statistically identified (e.g., any variable significantly linked with the outcome variables) confounding variables will be controlled for in the analytical model.

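### The models for both aims use PLV with no stated correction for its chance level, so a group difference in that level could appear as a difference in co-regulation

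*Protocol article*

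**What the plan says.** Under General and specific aims, the Protocol article singles out one index for the group comparison: "primarily, PLV measure". In Plan of statistical analyses, Aim 1 compares VPT and FT dyads on the co-regulation indices with general linear models. Aim 2 uses ANOVA with "dyadic brain-to-brain co-regulation indices as the dependent variable" and the three groups as factor. Neither model mentions a chance-corrected version.

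Table 4 describes the low end of the PLV scale thus: "values closer to 0 indicate random signals with unsynchronized phases".

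Surrogates appear once, in Estimating indices of inter-brain co-regulation, as a safeguard against spurious findings: "we will compare the synchronization indices obtained from the real dyads to surrogate data generated by randomly pairing mothers and infants from different dyads". They do not return in the statistical section.

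The number of epochs behind each dyad's value is not fixed. Pre-processing pipeline sets only a minimum: "Dyadic data will undergo further analyses if their signal contains at least 30 good epochs in both the Play and Reunion phases". Epochs rejected for either partner are dropped for both, so the count varies by dyad, and no equalisation is stated. With non-overlapping 1-second epochs, the laboratory procedure allows at most 120 epochs in Play, 60 in Still-Face and 120 in Reunion.

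The article does not say whether PLV is taken across epochs or over time within each epoch. The planned study of how each index evolves from epoch to epoch suggests the latter.

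**The concern.** PLV is the length of a mean vector, so it cannot be negative. With a finite amount of data it is above zero even when the two signals are unrelated. This chance level, or floor, depends on features that have nothing to do with coupling: the number of epochs when PLV is taken across them, and the rhythmicity of the signals when it is taken within them.

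A floor common to all groups would cancel in a group comparison. One that differs would not. Infants who move more lose more epochs, and VPT and FT infants might differ in the shape of their spectra. Either could give a group difference in PLV with no difference in co-regulation.

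The planned comparison with surrogates asks whether coupling exceeds chance. The models in the statistical section ask whether groups differ. The first question can be answered yes while a difference in floor drives the answer to the second.

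**Working it through.** **The plan's own figure.** The sample size uses f = 0.25, alpha 0.05, power 0.80 and three groups. For one-way ANOVA with N = 159, the noncentrality is 159 × 0.25² = 9.94 on 2 and 156 degrees of freedom. Power is 0.805, and 159 is the smallest multiple of 3 that reaches 0.80. The plan's figure ("The procedure yielded a total sample size of 159 subjects (53 subjects per RCT arm") is reproduced. This point does not change it. The 53 per group is used below.

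**Floor, PLV across n epochs, no coupling.** The expected value is √(π/(4n)).

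| Usable epochs | Formula | Simulated mean |
|---|---|---|
| 30 (minimum) | 0.162 | 0.162 |
| 60 (Still-Face maximum) | 0.114 | 0.115 |
| 80 | 0.099 | 0.100 |
| 120 (Play or Reunion maximum) | 0.081 | 0.081 |

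The floor doubles over the range that the plan admits for Play and Reunion.

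**Floor, PLV within 1-second epochs, no coupling.** Independent noise at 500 Hz, band-passed, with Hilbert phase, gave about 0.55 (3–5 Hz), 0.45 (4–7 and 6–9 Hz) and 0.40 (8–12 Hz). Here the floor does not depend on epoch count. False-positive rates stayed at 4.7% with 60 versus 70 epochs and 4.5% with 50 versus 70. It does depend on spectral shape. In the 6–9 Hz band, a sharper peak in one partner raised it from 0.45 to 0.48, and a peak in both partners raised it to 0.57–0.65.

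**Effect on a group test, across-epoch PLV.** Assumptions, none of them given in the article: mean usable epochs of 50 and 70, SD 15, 53 per group, one channel pair, no coupling.
- Floor difference: √(π/200) − √(π/280) = 0.1253 − 0.1059 = 0.0194.
- Sampling variance of PLV near 60 epochs: (1 − π/4)/60 = 0.00358.
- Added variance from epoch counts varying between dyads: the slope of the floor at 60 epochs is 0.1144/120 per epoch, times 15 = 0.0143, and squared = 0.00020.
- SD per dyad: √0.00378 = 0.0615. Standard error of the difference: 0.0615 × √(2/53) = 0.0119.
- Expected z: 0.0194/0.0119 = about 1.62. Rejection rate at two-sided 0.05: 1 − Φ(1.96 − 1.62) = about 37%.
- With a true between-dyad SD of 0.05, the variance is 0.00378 + 0.0025 = 0.00628 and the SD is 0.0793. Expected z is 1.26, and the rate is about 24%.

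Simulation agrees to within about three percentage points. Subtracting a surrogate PLV based on the same epoch count returned the rate to about 5%. With equal epoch counts, uncorrected PLV holds its level at about 5%.

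**Effect on a group test, within-epoch PLV.** In the 6–9 Hz band (53 per group, 75 epochs, one pair, 200 runs), a threefold group difference in infant peak power gave 21% false positives on uncorrected PLV. The rate was 3.5% after subtraction of same-group surrogates on equal epochs. A 1.5-fold difference gave no visible inflation.

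**The case against.** Several points on the other side stand.

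- **The larger rates belong to one implementation.** The planned epoch-by-epoch trends point towards within-epoch PLV. There, unequal epoch counts do no harm, and bias needs a substantial spectral difference.
- **No group difference is shown.** The article gives neither epoch counts nor spectra by group. The 50 versus 70 gap is an assumption.
- **Much higher rates would mislead.** Averaging four channel pairs raises the 37% to about 85%, and a reader might take that as the expected error. It needs independent pairs, whereas EEG channels are correlated, and it assumes that dyads do not truly differ. With a between-dyad SD of 0.05 it falls to about 39%.
- **The covariate rule may help.** Both aims adjust for variables found to be linked with the outcome. Adding epoch count as a linear covariate brought the across-epoch error to 5% or below. But epoch count is not named, its inclusion would depend on a significance screen, and it would not address spectral differences.
- **Silence on matching is not proof of its absence.** A reader might infer that surrogates are pooled over groups and phases. The article does not say so. Data are split by phase before segmentation, so same-phase pairing is a natural reading, and a fuller plan could specify matching.
- **Table 4 is not a claim that chance PLV is zero.** It describes the end of a scale, and planning surrogates suggests that zero is not relied on as the reference.

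What remains is a stated choice and not missing detail: the indices are the model outcome, and the surrogates are given the role of a check.

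**Conclusion.** The concern holds as a risk to the primary index. PLV has a floor well above zero under either way of computing it, the group models carry no stated correction, and a real-versus-surrogate comparison would not remove a floor difference between groups.

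The main exposure is the non-randomised FT versus VPT comparison, in Aim 1 and in the FT part of the Aim 2 ANOVA. A reader might infer that the trial's randomised contrast is equally affected. It is not: VPT-VF versus VPT-CU is affected only if the intervention or selective loss of EEG data changes artefact load or spectra.

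The size is conditional. For across-epoch PLV under the assumed 50 versus 70 gap, false positives are about 37% for one channel pair, or about 24% with a between-dyad SD of 0.05. For within-epoch PLV, the one scenario with inflation (21%) needed a threefold difference in peak power. The documents do not support saying that the results will be biased, only that the plan leaves them open to it. The change is worth making before group data are examined.

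**What to change.** 1. State whether PLV is computed across epochs or within each epoch and then averaged.
2. Make the outcome in both aims a surrogate-corrected index. For each dyad, phase, band and channel pair, take the real PLV minus the mean of its surrogates, or its z-score against their distribution.
3. Form the surrogates by pairing that infant and that mother with other partners from the same group and the same phase, on the same number of epochs.
4. Report uncorrected PLV as supportive, with usable epoch counts by group and phase.

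The cost is a little analysis code and computing time. Surrogates are already planned, and no new data or change in sample size is needed. The downside is slightly more variable scores and a less familiar scale.

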### Statistical power and sample size estimates

The sample size has been estimated according to over-arching Aim 2, setting parameters as follows: medium effect size, *f* = 0.25, *alpha* = 0.05, *beta* = 0.20, number of groups = 3 (VPT-VF, VPT-CU, and FT). The procedure yielded a total sample size of 159 subjects (53 subjects per RCT arm). Nonetheless, considering the longitudinal nature of the study and the attrition rate related to EEG tasks with infants, an oversampling of *n* = 80 (~ +50%) subjects per RCT arm was planned to secure the minimum sample size for appropriately powered statistical analyses.

### Plan of statistical analyses

#### Preliminary analyses

##### Specific aim 1

General linear models (GLMs) will be carried out to compare VPT and FT dyadic brain-to-brain co-regulation indices during the experimental procedure phases. Theoretically relevant (e.g., gestational age) and statistically identified (e.g., any variable significantly linked with the outcome variables) confounding variables will be controlled for in the analytical model.

##### Specific aim 2

Separate analyses of variance (ANOVA) will be used with dyadic brain-to-brain co-regulation indices as the dependent variable and groups (FT, VPT-VF, and VPT-CU) as the independent variable. Theoretically relevant (e.g., gestational age) and statistically identified (e.g., any variable significantly linked with the outcome variables) confounding variables will be controlled for in the analytical model.

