## Methods and procedures

### Study design and procedures

The 2-BRAINED project is a randomized-controlled trial (RCT) with three arms. The first arm includes VPT infants and their caregivers randomly allocated to the intervention arm (VPT-VF). The second arm includes VPT infants and their caregivers randomly allocated to the care as usual arm (VPT-CU). This arm will act as a control group matched to preterm conditions of VPT-VF. The third arm includes FT infants and their caregivers and will act as an additional control group unmatched by preterm conditions. Both VPT-CU and FT arms will receive no VF intervention.

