#### Study timeline

The 2-BRAINED study features five data collection waves (see Figure 1). The VF intervention is delivered after wave T1 (NICU discharge) and before wave T2 (3 months CA) to subjects allocated to the VPT-VF arm. The EEG-hyperscanning task will occur for all subjects at wave T4 (9 months CA) and will feature the videotaping of mother–infant interaction according to a modified Face-to-Face Still-Face (FFSF) procedure (Tronick et al., 1978) and the simultaneous EEG data collection from both the interactive partner. At each wave, parents will receive questionnaires by email using REDCap.^1^

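### Aim 1 compares VPT with FT dyads after half of the VPT dyads have had VF, so the estimated preterm deficit shrinks as the intervention succeeds

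*Protocol article*

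**What the plan says.** Under General and specific aims, Aim 1 looks for differences in co-regulation indices "between dyads of caregivers and VPT compared to FT infants". The hypothesis is that VPT dyads "would show less strong brain-to-brain co-regulation indices compared to dyads of FT counterparts at 9 months". The analysis section (Specific aim 1) repeats the comparison without naming arms: "General linear models (GLMs) will be carried out to compare VPT and FT dyadic brain-to-brain co-regulation indices during the experimental procedure phases". The covariates are gestational age, as an example of a theoretically relevant variable, and variables found to be related to the outcome. VF allocation is not mentioned. Specific aim 2, directly below, does list FT, VPT-VF and VPT-CU as separate groups.

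Study timeline places the intervention early: "The VF intervention is delivered after wave T1 (NICU discharge) and before wave T2 (3 months CA) to subjects allocated to the VPT-VF arm". Hyperscanning comes only at T4, 9 months corrected age, and no earlier wave includes it. For Aim 2, which compares VPT-VF with VPT-CU on the same indices, the authors write: "we hypothesize to describe greater brain-to-brain co-regulation in the former group". Planned arm sizes are equal: a minimum of 53 and an enrolment of 80 per arm.

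**The concern.** Aim 1 asks how far VPT birth and the NICU experience lower mother–infant co-regulation. The natural answer is the gap between FT dyads and VPT dyads under usual care. The stated VPT group is instead a half-treated mixture, because there is no EEG measure before VF and no separation of the arms.

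The two aims then work against each other. The better VF works, the smaller the Aim 1 difference becomes, both as an estimate and as a test. The result also depends on the allocation ratio of the trial, which has nothing to do with prematurity. A null or small Aim 1 result could mean that there is no preterm deficit, or that there is one and VF repaired part of it. Enrolling more dyads does not remove the bias. The Discussion also promises estimates of how much inter-brain synchrony to expect in typical and atypical development, and a mixed VPT mean does not supply them.

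**Working it through.** **Inputs from the protocol.** Three arms of equal size; 53 per arm as the minimum and 80 enrolled; f = 0.25, alpha = 0.05, beta = 0.20 (Statistical power and sample size estimates). VF is given between T1 and T2, and the outcome is measured at T4 (Study timeline). VF is expected to raise the outcome (Aim 2).

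**Assumed, because the documents do not give them.** D, the FT minus VPT-CU difference in within-arm SD units; and r, the share of D that VF recovers.

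**Step 1: the plan's own figure.** One-way ANOVA with 3 groups, noncentral F with noncentrality f²N. Power is 0.799 at N = 157 and 0.802 at N = 158. Rounding up to equal arms gives 159, where noncentrality is 0.0625 × 159 = 9.94 and power is 0.805. The stated 159 (53 per arm) reproduces. It concerns the three-group test, not the Aim 1 contrast.

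**Step 2: what the pooled contrast estimates.** VPT-CU lies D below FT and VPT-VF lies D(1 − r) below FT. With equal arms the pooled deficit is ½D + ½D(1 − r) = D(1 − r/2). The shortfall, rD/2, is half the VF effect. The estimate is 12.5% too small at r = 0.25, 25% at r = 0.5 and 50% at r = 1.

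**Step 3: power at D = 0.5 SD.** Two-sided t-test, alpha 0.05, noncentrality d√(n₁n₂/(n₁ + n₂)), no covariates. The pooled contrast has d = 0.5(1 − r/2) with 2n versus n dyads; VPT-CU versus FT has d = 0.5 with n versus n. Example at r = 0.5 and n = 53: d = 0.375, noncentrality 0.375 × √(106 × 53/159) = 0.375 × 5.944 = 2.229, power 0.601.

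| r | Pooled difference (SD) | Pooled power, 106 vs 53 | Pooled power, 160 vs 80 |
|---|---|---|---|
| 0 | 0.500 | 0.840 | 0.953 |
| 0.25 | 0.438 | 0.734 | 0.889 |
| 0.5 | 0.375 | 0.601 | 0.779 |
| 0.75 | 0.313 | 0.455 | 0.623 |
| 1 | 0.250 | 0.315 | 0.444 |

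VPT-CU versus FT has power 0.722 at 53 per arm and 0.882 at 80 per arm, whatever r is. With the error variance of the three-group model, the 53-per-arm figure becomes 0.725.

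The table uses the within-arm SD. Merging two VPT arms with different means also widens the spread of the VPT group; allowing for that lowers the pooled power slightly, for example to 0.596 at r = 0.5 and 0.304 at r = 1 with 53 per arm.

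**Step 4: break-even.** At 53 per arm the two contrasts have equal power at r = 0.273. The large-sample formula agrees closely: 2(1 − √0.75) = 0.268. Pooling wins on power only below that, and is biased for any r above 0.

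**Step 5: other values of D.** At D = 0.3 and 53 per arm, pooled power is 0.426 at r = 0 and 0.14 at r = 1, against 0.334 for VPT-CU versus FT. Choosing group means that give exactly the protocol's f = 0.25: with r = 0.5 (D = 0.61), 0.77 pooled against 0.88; with r = 1 (D = 0.53), 0.35 against 0.77.

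**The case against.** The text never says in so many words that the VPT arms are merged. The list of covariates is open-ended, and an allocation term in the model would turn the VPT coefficient into the usual-care contrast. A condensed article may leave contrast coding to a fuller document. This part does not stand: Aim 2 names the three arms and Aim 1, one paragraph earlier, does not. Pooling is the plain reading, and a general clause about confounders does not supply an allocation term.

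The planned three-group ANOVA already contains FT versus VPT-CU, so no information is lost. That is true and makes the repair cheap, but the protocol does not assign that contrast to Aim 1.

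The bias needs VF to act, and still to be visible about six months later. If it does nothing, pooling is unbiased and more powerful. If it works as hypothesised, the error is toward zero and would not create a false deficit. This stands, but the trial rests on the hypothesis that VF works, and choosing the contrast after seeing the VF result would be data-driven.

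The power figures rest on assumed D and r and ignore the planned gestational-age adjustment. VPT infants are below 35 weeks and FT infants at 37 weeks or more, so that covariate fully separates the groups. This stands as a limit on the figures: they are unadjusted. It is a separate problem, which neither removes the dilution nor is solved by changing the contrast.

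Finally, Aim 1 is not randomised, the sample size was set for Aim 2, and the randomised VF comparison is untouched. That bears on how serious the point is, not on whether it is right.

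**Conclusion.** The concern holds. Under the plain reading of the Aim 1 analysis, the VPT–FT contrast understates the usual-care deficit by half of whatever effect VF has. That factor follows from equal arms alone. It assumes only that the deficit of interest is the one under usual care and that VF acts in the hypothesised direction.

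The loss of power depends on the assumed D and r. At 0.5 SD and 53 per arm, restricting Aim 1 to VPT-CU is the stronger test once VF recovers more than about 27% of the deficit. The oversampling to 80 per arm raises power for both contrasts but leaves the bias unchanged. The randomised comparison in Aim 2 is not affected.

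**What to change.** - Define the Aim 1 primary contrast as FT minus VPT-CU, estimated from the same three-group model as Aim 2 so that all dyads contribute to the error variance.
- Report FT minus VPT-VF as a separate contrast showing how far treated VPT dyads approach FT dyads.
- Keep pooled VPT versus FT, if wanted, as a labelled secondary analysis, with a note that it averages treated and untreated dyads.
- State the power of the Aim 1 contrast for 53 versus 53 and the difference assumed.

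The change is to wording only: no new data, visits or enrolment. The cost is lower power if VF has no effect: 72% instead of 84% for 0.5 SD at 53 per arm, or 88% instead of 95% if all 80 per arm are retained. The contrast should be fixed before any outcome data are examined by arm. How gestational age enters the Aim 1 model needs separate attention.

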#### Population, enrollment, and arm allocation

VPT and FT infants will be enrolled at birth by contacting their caregivers within the first 48 h after delivery. Informed consent will be obtained. VPT infants will be considered eligible in the presence of the following conditions, as reported in medical charts: gestational age below 35 weeks, absence of major brain lesions as documented by cerebral ultra-sound, no neuro-sensory deficits including retinopathy of prematurity (ROP) equal or above stage 2, absence of genetic syndrome, or malformations involving the central nervous system. FT infants will be considered eligible if they meet the following conditions: a gestational age of 37 weeks or more, are healthy, and show no evident signs of neurodevelopmental risk or morbidities. For both groups, exclusion criteria will include single-parent families, parental age under 18 years, lack of Italian language mastery, and the presence of documented psychiatric disorders.

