### Sources of bias and mitigation strategies

The heterogeneity of VPT infants’ conditions should not be underestimated. Even in the absence of severe comorbidities and brain injuries, the experience of NICU hospitalization might be very different for each infant and their parents. To avoid extreme variations, the gestational age range will be constrained between 28 and 35 weeks. Moreover, stress related to the NICU environment will be evaluated and quantified with a well-validated questionnaire (Miles et al., 1993). Selection issues might affect random allocation plans in RCT arms. The allocation to VPT-VF and VPT-CU arms will occur by using an automatically generated list of binary codes that will be consecutively matched with the enrolled families across consecutive sampling. This will reduce the risk of self-selection. To further avoid confounding by infant sex and assure sex distribution balancing, the random allocation will be stratified by infant sex by *post-hoc* controls every 20 enrollments. Parental gender will also be unconstrained, inviting the primary caregiver—and not explicitly the mother—to participate in the study, VF intervention, and observational procedures. EEG procedural steps and artifacts might easily result in the loss of subjects in a longitudinal study; a 50% oversampling was planned to achieve the minimum sample size for adequately powered statistical analyses.

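### Gestational age is named as a confounder in the very preterm versus full-term model, but it defines those two groups without overlap, so adjusting for it strips out or blurs the Aim 1 difference

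*Protocol article*

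**What the plan says.** In the protocol article, Plan of statistical analyses, Specific aim 1 states: "General linear models (GLMs) will be carried out to compare VPT and FT dyadic brain-to-brain co-regulation indices". Its next sentence commits the model to controlling for confounders that are "Theoretically relevant (e.g., gestational age) and statistically identified". Gestational age is the only example given of a theoretically relevant confounder. The sentence is repeated under Specific aim 2, where the model is an analysis of variance across FT, VPT-VF and VPT-CU.

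The section Population, enrollment, and arm allocation defines the groups by the same variable: "gestational age below 35 weeks" for VPT infants and "a gestational age of 37 weeks or more" for FT infants. The section Sources of bias and mitigation strategies gives the VPT limits a second time: "the gestational age range will be constrained between 28 and 35 weeks".

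The Aim 1 hypothesis is that "VPT infants and their caregivers would show less strong brain-to-brain co-regulation indices compared to dyads of FT counterparts".

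**The concern.** A confounder affects the outcome and is distributed differently between the groups, but it must vary within each group over a shared range if adjustment is to compare like with like. Gestational age has no shared range here. Under either statement of the VPT limits, no VPT infant has a gestational age found among FT infants, and nobody is enrolled between 35 and 37 weeks. Group membership is a function of gestational age.

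Holding gestational age fixed while changing group therefore asks for a comparison that no pair of dyads in the study can supply. The model answers it by extrapolating the within-group slope across the gap. The result is not the VPT–FT difference that Aim 1 hypothesises. If co-regulation falls off gradually with prematurity, the hypothesis can be true and the adjusted test still comes out null.

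**Working it through.** **The plan's own figure.** Statistical power and sample size estimates gives f = 0.25, alpha 0.05, power 0.80, three groups, total 159. With noncentrality N·f² and (2, N − 3) degrees of freedom, N = 159 gives power 0.805 and N = 156 gives 0.797. The 159 reproduces for an analysis of variance without covariates. The sample size is not at fault.

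**Inputs.** From the document: the group limits, and 53 analysable dyads per arm. Assumed, because the document does not give them: uniform gestational age within groups (28–35 and 37–41 weeks as base case), a true VPT–FT difference of −0.5 SD, and either 106 versus 53 dyads (both VPT arms pooled) or 53 versus 53 (one VPT arm). The plan does not say whether treated VPT dyads enter Aim 1.

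**What the adjusted coefficient estimates.** With pooled within-group slope b, it is (mean outcome VPT − mean outcome FT) − b × (mean gestational age VPT − mean gestational age FT). The base-case mean ages are 31.5 and 39, a gap of −7.5 weeks.

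- Deficit fully graded with gestational age: b = 0.5/7.5, so the coefficient is −0.5 − (0.5/7.5)(−7.5) = 0. Simulated rejection is about 5%, against about 84% unadjusted.
- Half graded, half step: −0.5 − (0.25/7.5)(−7.5) = −0.25. Simulated rejection is about 10% with 106 versus 53.
- Pure step: b = 0, so the coefficient stays at −0.5. Only precision is lost.

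**Loss of precision.** The variance inflation factor (VIF) is 1/(1 − R²) = (W + B)/W. W is the weighted within-group variance of gestational age. B is p(1 − p) × gap², with p the VPT share. For 106 versus 53, p = 2/3:

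- W = (2/3)(7²/12) + (1/3)(4²/12) = 2.72 + 0.44 = 3.17
- B = (2/9)(7.5²) = 12.50
- R² = 12.50/15.67 = 0.80; VIF = 4.95; standard error × √4.95 = 2.22

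The unadjusted standard error is √(1/106 + 1/53) = 0.168 SD, so the noncentrality is 0.5/0.168 = 2.97 and power is 84%. Adjusted, it is 2.97/2.22 = 1.34 and power is 26%.

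For 53 versus 53: W = 2.71, B = 0.25 × 56.25 = 14.06, VIF = 6.19, standard error × 2.49. Noncentrality falls from 2.57 to 1.03, and power from 72% to 18%.

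Other assumed distributions (106 versus 53, pure step):

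| VPT / FT weeks | W | B | VIF | SE × | Adjusted power |
|---|---|---|---|---|---|
| 28–35 / 37–41 | 3.17 | 12.50 | 4.95 | 2.22 | 26% |
| 24–35 / 37–41 | 7.17 | 20.06 | 3.80 | 1.95 | 33% |
| 32–35 / 37–41 | 0.94 | 6.72 | 8.12 | 2.85 | 18% |
| 28–32 / 37–42 | 1.58 | 20.06 | 13.67 | 3.70 | 13% |

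The last row is an extreme in which recruitment uses only the lower part of the VPT range.

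**Aim 2, three-group model (53 per arm, FT taken as 37–42 weeks).** With gestational age added, the VIF is 1.01 for VF versus CU and 4.2 for FT versus CU. Omnibus power at f = 0.25 falls from 0.80 to 0.21 when the signal is FT against both VPT arms. It falls to 0.40 when the means are equally spaced with VF midway, and stays at 0.80 when the signal is VF versus CU only.

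**The case against.** Several points on the other side deserve weight.

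*Gestational age is only an example, and details can wait for the analysis plan.* It is the sole example of a theoretically relevant covariate. It stands under the aim where it does harm, and it is tied to a commitment to control for it. Nothing in the article limits it to the VPT arms or centres it. A choice already made badly is not cured by leaving the rest for later.

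*The adjustment does not always remove the effect.* This stands. A reader might infer that Aim 1 is bound to come out null. The document does not support that, because it does not say how co-regulation depends on gestational age. A pure step survives without bias if the linear model holds, although at much lower power.

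*Gestational age is a sensible covariate for the randomised comparison.* This stands too. It is prognostic, it overlaps fully between VF and CU, and adjusting for it costs that contrast almost nothing. A reader might infer that the repeated sentence undermines the randomised result. The VIF of 1.01 shows that it does not.

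*The numbers rest on assumptions.* They do, and the pooling of VPT arms is one of them. The direction does not depend on them, but the exact percentages do. The standard error does not always more than double: the eligibility section sets no lower limit, and a 24–35 week spread gives a factor of 1.95.

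*Birth weight, NICU stay and NICU-related parental stress.* A reader might extend the criticism to these. The Measures section lists them as data collected, and the analysis section does not name them as covariates. They could enter only through the rule that admits variables associated with the outcome.

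**Conclusion.** The concern holds for every contrast between VPT and FT dyads. By the document's own limits, gestational age is the exposure in Aim 1, and adjusting for it changes the question. The part of the difference that tracks gestational age disappears from the group coefficient. What remains depends on linear extrapolation over an unobserved gap and has a standard error roughly 2 to 3 times larger, or more if VPT recruitment is narrow.

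The percentages are illustrations of size under the stated distributions and the 0.5 SD difference. The non-overlap comes from the document and needs no assumption.

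Under Aim 2 the harm is confined to the FT contrasts and to an omnibus test driven by FT. The randomised VF-versus-CU contrast is essentially untouched. This should be corrected before analysis, because one of the two main aims can fail for a reason unrelated to its hypothesis.

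**What to change.** State that no VPT-versus-FT contrast, in Aim 1 or Aim 2, is adjusted for gestational age. Use gestational age only for VF versus CU. Either fit a VPT-only model with it as a baseline covariate, or keep the three-group model and centre gestational age within the VPT group as a whole (both arms together) and within the FT group. Centring leaves the group means free to carry the VPT–FT difference while still adjusting VF against CU.

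For FT contrasts, limit the rule on statistically identified covariates to variables that are measured in both groups and overlap between them. Parental NICU stress, collected in VPT families only, would then not be eligible.

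State also whether VPT-VF dyads are pooled into Aim 1, since its power depends on this.

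The cost is a change of wording in the analysis section and no new data. The small downside is that VF versus CU may need its own VPT-only model or a centred covariate, neither of which the article now describes.
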